### Methods in analysis to handle protocol non-adherence and any statistical methods to handle missing data {20c}

If parts of the protocol need to be changed, this will always occur in consultation with the study management and the cooperation partners. The final decision on any changes will be made by the study management. Missing data should be minimised by the online survey. However, if this should occur, the procedure of multiple imputation will be chosen.

### Plans to give access to the full protocol, participant-level data, and statistical code {31c}

The datasets analysed during the current study and statistical code are available from the corresponding author on reasonable request, as is the full protocol (note: this is only possible if the school board in charge approves this).

### Composition of the data monitoring committee, its role, and reporting structure {21a}

As the trial will not be conducted in patients or any at-risk group, and as its duration is relatively short (time from the first to last data assessment is 6 months), there will not be a data monitoring committee (DMC). In addition, the trial cannot be modified once the intervention group has started. Of course, after each data assessment, we will check whether everything has ensued satisfactorily. There are no competing interests and the data are independent from the sponsor.

### Adverse event reporting and harms {22}

We do not expect any harms caused by the questionnaires or the prevention programme itself. However, we do offer consulting for students who are in need of a higher level of psychiatric care. The Department of Child and Adolescent Psychiatry, Neurology, Psychosomatics and Psychotherapy, University Medical Centre Rostock, can offer appointments locally and the University Hospital of Wuerzburg, Center of Mental Health, Department of Child and Adolescent Psychiatry, Psychosomatics and Psychotherapy, can offer consulting appointments online. Furthermore, the webpage and the brochure every student receives contain numbers of hotlines, where help is available 24/7. If any adverse events occur during the time of the trial, we will collect and document them and report the type of event as well as the managing process. Furthermore, during the training, teachers will be instructed about dysfunctional coping behaviour and how to deal with this in terms of the dialectical behavioural therapy for adolescents (DBT-A).

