## Interventions

### Explanation for the choice of comparators {6b}

In prevention research, a comparison of an intervention group and a waiting list control group is common for ethical reasons [42]. In order to test the effectiveness of a universal prevention program, comparing these two groups seems reasonable and cost-effective. As we will be working with adolescents, we will ensure that every school in the waiting list control group will be offered the intervention directly after the final assessment (6-month follow-up), enabling all adolescents to eventually benefit from the programme.

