
### Criteria for discontinuing or modifying allocated interventions {11b}

All participating schools will be supported by our study team during the implementation of the programme. Experience from other studies conducted in schools has shown that weekly contact by email and telephone is a good way to stay in touch and to clarify questions quickly. Through regular exchange and contact with the teachers carrying out the programme, difficulties should be detected and corrected in advance in order to improve adherence.

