### Strategies to improve adherence to interventions {11c}

#### Adherence

Each participating school (and especially the staff) will receive online training before administering the programme. This training will focus on the implementation of the PowerPoint presentation guiding the lesson and will also refer to the booklet. Furthermore, two to three small role-plays on crises will be carried out to prepare the teachers for all eventualities, such as students reporting non-suicidal self-harm to the teachers or students becoming highly stressed (e.g. starting to cry, needing to leave the room). To check adherence during the intervention, we will ask the school staff to fill out an online survey measuring their adherence to the given instructions. Questions will be asked about the presentation itself, how well students have understood the topics, whether everything was discussed, what questions remained, how easy it was for the teachers, and how well they think the class liked it.

In a next step, this information should be used in order to improve the presentation if necessary.

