### Procedure for unblinding if needed {17b}

Not applicable. Due to the study design, schools and participants will know the group to which they have been assigned. However, to avoid manipulation of the questionnaires, participants will be unaware of the study hypotheses. The WL control group will merely be told that the intervention will take place in 6 months and that data will be collected in the interim.

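### Adverse events are recorded only as they come to notice, and training and support that aid detection appear to reach only intervention schools, so event counts are not a fair harm comparison between arms

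*Protocol article*

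**What the plan says.** Under Adverse event reporting and harms {22}, the protocol expects no harm from the questionnaires or the programme and then says "If any adverse events occur during the time of the trial, we will collect and document them". It adds that the kind of event and its handling will be reported. The sentence is not limited to one arm. It names no reporter and no schedule of enquiry, and it plans no comparison between arms. The same section says that "during the training, teachers will be instructed about dysfunctional coping behaviour".

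The training is described under Adherence {11c}: "Each participating school (and especially the staff) will receive online training before administering the programme". It includes crisis content: "two to three small role-plays on crises will be carried out to prepare the teachers for all eventualities", with disclosed self-harm and acute distress as the examples. Section {11b} says "All participating schools will be supported by our study team during the implementation of the programme", and "Through regular exchange and contact with the teachers carrying out the programme, difficulties should be detected".

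For the waiting-list arm, section {6b} says that "every school in the waiting list control group will be offered the intervention directly after the final assessment (6-month follow-up"). Until then, section {17b} says, "The WL control group will merely be told that the intervention will take place in 6 months" and that data are being gathered meanwhile. There is no blinding ({17a}).

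**The concern.** Where events are recorded only when noticed, the count in each arm is the true number multiplied by the share noticed. If staff in one arm have rehearsed crises, been taught about dysfunctional coping and are in touch with the study team, while staff in the other arm are not, the noticed share will probably differ even when the true risk is the same.

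An error is possible in either direction. Better detection in intervention schools can look like harm from the programme. A real excess can equally be put down to better detection, because no comparable waiting-list rate exists to set against it. The trial has no data monitoring committee, and these recorded events are the only evidence that the protocol designates as harms.

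**Working it through.** The documents give no adverse-event rate and no detection rate, so there is no stated figure to reproduce. The check is textual, followed by an illustration under assumed rates.

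**Step 1. Who has which aid to detection during the 6 months?**

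| Element | Tied to | Waiting-list schools before T3 |
|---|---|---|
| Crisis role-plays, coping instruction ({11c}, {22}) | Training before delivery of the programme | Not reached, by timing ({6b}) |
| Study-team support, detection of difficulties ({11b}) | Period of delivery; teachers who deliver | Not reached, by timing ({6b}) |
| Monthly feedback ({18b}) | No arm | Reached, but described as outgoing news, reminders and small gifts |
| Check after each assessment ({21a}) | No arm | Reached, but not described as a harms enquiry |
| Offers of appointments ({22}, {30}) | No arm | Reached, but relies on students coming forward |

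The first two rows are an inference. Sections {11b} and {11c} speak of all or each participating school, but both tie the activity to delivering the lesson, and waiting-list schools do not deliver it within the comparison period.

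**Step 2. Could the questionnaires feed the event count?** Not for individual students. Section {18a} uses self-generated codes, and sections {19} and {27} rule out any list linking codes to names. The team cannot follow a worrying answer back to a student, so events must surface through school staff or through students seeking help.

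**Step 3. What would unequal detection do?** Recorded events = n × true risk × share detected. With the same n and the same true risk in both arms, the recorded ratio reduces to (share detected, intervention) ÷ (share detected, waiting list), whatever the true risk.

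Take n = 1894 ÷ 2 = 947 students per arm. This assumes that 1:1 allocation of schools gives equal student numbers. True risks of 2% and 5% and all detection shares are assumptions.

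| Detected, intervention vs waiting list | Events at 2% | Events at 5% | Recorded ratio (true ratio 1) |
|---|---|---|---|
| 80% vs 80% | 15.2 vs 15.2 | 37.9 vs 37.9 | 1.0 |
| 80% vs 60% | 15.2 vs 11.4 | 37.9 vs 28.4 | 1.33 |
| 80% vs 40% | 15.2 vs 7.6 | 37.9 vs 18.9 | 2.0 |
| 60% vs 20% | 11.4 vs 3.8 | 28.4 vs 9.5 | 3.0 |

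For example, 947 × 0.02 × 0.80 = 15.2 and 947 × 0.02 × 0.40 = 7.6.

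**Step 4. What is measured alike in both arms?** Section {13} gives every participant the full battery at baseline, T2 and T3. This includes PHQ-4, self-injury, insomnia and eating-disorder symptoms. Section {20a} lists these as secondary outcomes for the comparison of change between arms. No section names any of them as a harm measure.

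**The case against.** The strongest reply is that the protocol plans no comparison of adverse-event counts. It promises a descriptive account, and no section draws a conclusion of harmlessness from it. This stands: the fault is not a wrong analysis but a count that invites a comparison it cannot carry.

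Second, the reporting channel is not named, and some routes are open to both arms. This also stands, so the text supports likely unequal ascertainment and not certain inequality. The open routes are not described as harms enquiries, however, so they do not restore balance.

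Third, the support in {11b} serves adherence and belongs to the delivery of one 90-minute lesson within 21 days of baseline. Weekly contact is mentioned there as good experience from other studies, and nothing says that it runs for six months. The asymmetry in contact may therefore be short. The training, once given, is not undone.

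Fourth, a reader might infer that the trial cannot tell programme harm from background. The documents do not support that. PHQ-4 and self-injury are collected identically in both arms, section {12} adds three-level ratings for each questionnaire, and section {20b} plans healthy versus clinically relevant subgroups. The limitation belongs to the event counts alone. None of these analyses, though, is directed at individual worsening as a harm.

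Finally, a journal article leaves much harms detail to the full protocol. That excuses missing detail on reporters and tabulation. It does not remove the imbalance created by when training and support are given, and an analysis plan cannot later recover waiting-list events that nobody asked about.

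**Conclusion.** The point holds in a limited form. Event-driven adverse-event counts in this unblinded trial are likely to be unequally ascertained between arms and should not be read as a comparison of harm. This rests on two assumptions: that training and delivery support follow the timing of the programme, and that at least some events reach the study team through school staff. Neither is stated outright.

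The direction is plausible and the size is unknown. The ratios of 1.33 to 3.0 merely restate the assumed detection shares and are not estimates for this trial. A reader might take them as evidence that a false harm signal will appear; the documents give no basis for that.

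The measures needed for a more even comparison are already being collected. What is lacking is their designation as harms. This is a cheap improvement, not an error in the primary analysis.

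**What to change.** In section {22}, add two provisions.

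1. Report harms by arm from the questionnaires, from baseline to T2 and to T3:
   - the proportion moving to a higher PHQ-4 band;
   - new onset of self-injury (entry answer changing from No to Yes), together with increased DSHI-9 frequency among those answering Yes at baseline;
   - the distribution of PSS-10 worsening.

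   Give 95% confidence intervals that allow for clustering by school. The frequency element is needed because the entry question in {18a} asks about lifetime self-injury, so students who already answer Yes cannot show worsening on it.

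2. Put the same adverse-event question to the contact person of every school in both arms at baseline, T2 and T3. List events found through programme training or support contacts separately. Present all school-reported counts descriptively, with the caveat that trained and untrained staff may detect events differently.

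The second provision narrows the detection gap but does not close it, because the staff who answer still differ in training. The first does not depend on staff noticing anything. It remains self-report in an unblinded trial, and a student already in the top PHQ-4 band cannot move higher.

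The cost is a few lines of text, one extra table from data already collected, and one short question to schools that are already to receive monthly feedback.

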### Frequency and plans for auditing trial conduct {23}

There will be team meetings on a monthly basis within the members of the working group. Audits with the cooperation partners and with the sponsor will take place if necessary, but at the latest after the last follow-up at 6 months.

### Plans for communicating important protocol amendments to relevant parties (e.g. trial participants, ethical committees) {25}

Any modifications to the protocol will require a formal amendment to the ethics committee in Rostock as well as the Ministry of Education of Rostock.

## Dissemination plans {31a}

We plan to report all results, no matter the outcome following the guidelines of good scientific practice. Furthermore, we will endeavour to give easy access to the prevention programme *LessStress* for use in other schools.

## Discussion

According to the latest figures, over 20 million people in Germany are affected by mental illness (prevalence of 27.8%), including 2.7 million children and adolescents [92]. The goal of universal prevention is to increase competencies within a large population without prior selection. We want to contribute to this through the prevention programme *LessStress*. The advantages of *LessStress* lie in its short implementation time, the integration into normal school lessons, and the easy training of already existing school staff. If effects can be proven, a step would be taken towards keeping children and adolescents healthy in the school setting. If *LessStress* does not prove to be effective, it is important to find out what we can improve to bring scientifically evaluated and effective prevention programmes into schools. At the same time, some of the benefits of *LessStress* should also be seen as limitations. In particular, the short implementation time and the implementation by teachers may influence our outcomes. Moreover, the different schools with different requirements for the students could have a negative impact on this study. However, with our adjusted case number estimation, even small effects will be visible, insofar as they exist.

## Trial status

Protocol version 1, 04 November 2021

Start recruitment: 1 October 2022

Approximate date when recruitment will be completed: July 2023

## Data Availability

All principal investigators will be given access to the cleaned data sets. As this is a multicentre study, only the steering group has access to the full trial dataset. The data will remain on the server of the Data Centre of the University of Wuerzburg, where it will be safe, crypted, and not available for third parties. Any data required to support the protocol can be supplied on request, if the School Board in charge approved this.

## Abbreviations

CD-RISC 10: Connor-Davidson Resilience Scale
DERS-SF: Difficulties in Emotion Regulation Short Form
DMC: Data Monitoring Committee
DSHI-9: Deliberate Self-Harm Inventory 9-item version
FAS III: Family Affluence Scale
GAD-2: Generalized Anxiety Disorder Screening with 7 items
GDPR: European Union’s General Data Protection Regulations
HrQoL: Health-related quality of life
ICC: Intraclass correlation coefficient
IG: Intervention group
ISI: Insomnia Severity Index
KKH: Kaufmännische Krankenkasse
MBSR: Mindfulness-based stress reduction
PHQ: Patient Health Questionnaire
PSS-10: Perceived Stress Scale 10-item version
QoL: Quality of life
RCT: Randomised controlled trial
SCS: Self-Compassion Scale
SEED: Short Evaluation of Eating Disorders
SISE: Single-Item Self-Esteem
SFF: Schutzfaktoren Fragebogen (protective factors questionnaire)
WHO-5: World Health Organization 5 items for Well-Being
WL: Waiting list
